**Research Plan:** We plan to conduct a randomized, comparative effectiveness design trial, with 1:1 randomization. This will be done at two IHS clinical sites in the Gallup Service Unit at Indian Health Service: Gallup Indian Medical Center (GIMC) and Tohatchi Health Clinic (THC), with the plan to expand to Fort Defiance Medical Center and/or Shiprock Medical Center if we are unable to enroll our target sample size.

**Study Population:** All patients 18 years of age or older, with diagnosis of heart failure based on ICD code I50\* with a hospitalization (any cause) in the last 12 months. Only patients with active prescription through IHS and engaged in care at our centers (clinical visit within last 12 months) will be included. We will exclude patients on hospice care or those residing in an acute care or skilled nursing facility, or any patient currently residing outside of the 50-mile IHS Gallup Service Unit catchment area.

**Subject Recruitment:** Eligible patients are identified through a query through iCARE, a EHR based data system through the IHS EHR. Patients with ICD10 diagnostic criteria for HF will be identified (ICD10\*). The inclusion criteria will be all adults  $\geq 18$  years, who have a prescription in the IHS system in the last 12 months and have had a clinical visit at GIMC or THC in the last 12 months, as well as a hospitalization (all-cause) in the last 12 months. Patients will be consented verbally either at the health center or verbally over the phone to enroll. If we have not met our 50% enrollment goal by 6 months, we will expand enrollment to another Navajo IHS site—Fort Defiance and/or Shiprock Medical Center, and enroll patients with ER visit (rather than just hospitalization) in the last 12 months.

**Enrollment:** All patients that meet eligibility criteria and consent to participate will be enrolled to receive meal delivery simultaneously: all enrolled patients will start receiving the intervention at the same starting time point,  $t=0$ . Patients randomized to usual care will also start the “intervention” of usual care at the time  $t=0$ , so that all patients will have outcome assessment on the same time schedule. For operation and logistical considerations, all baseline assessment (including consent, enrollment, baseline surveys and lab work) will occur in the enrollment period (-45 to 0 days prior to the intervention period). No clinical events will be included during the enrollment period as an outcome.

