## - Phase II: Comparativeness effectiveness trial of Medically and traditionally tailored meals for Heart Failure

We will conduct a comparativeness effectiveness trial to evaluate the impact of providing medically and culturally tailored Indigenous focused meals delivered to heart failure patients. Meals will be prepared, packaged, and delivered once weekly, with delivery mechanism based on community and patient preference. Two meals will be provided daily for 60 days. Along with the meals, patients will also receive recipe cards with each meal, as well as educational information regarding the meals, traditional food items included, and nutritional information, to educate on the health benefits of the food provided, as well some information regarding the traditional foods included and from where they were sourced. Additionally, patients will receive one cooking class conducted by a Diné Registered Dietician ([name]) to learn how to make a few key recipes from the meal plan, all utilizing locally available ingredients.

**Baseline Characteristics:** In addition to the American Heart Association sociodemographic core measures, we will also collect tribal affiliation, language, and in which local chapter/community patients reside.

**Endpoints:** The primary outcome for the trial will be the proportion of patients who have a hospitalization or ER visit for any cause within 90 days post intervention period (all patients will start the study at t=0 as described above). We will not include hospitalizations that occur electively for an elective procedure.

Secondary outcomes will include: heart failure hospitalizations specifically, ER visits for volume overload specifically (ER visits for lower extremity edema, dyspnea, with clinical evaluation consistent with volume overload), change in weight and body mass index at 60 days from baseline, Kansas City

Cardiomyopathy Score (and its components including summary score, physical limitation score, symptom frequency score, quality of life score and social limitation score)[10], and the following lab parameters and biomarkers at baseline and at 60 days: albumin, prealbumin, creatinine, NT-proBNP, HbA1c, Total cholesterol, LDL-C, HDL-C, Triglycerides, CRP, urine albumin:creatinine ratio. Lab work will be permitted to be collected 14 days before 60 days mark and up to 30 days after (from 46 days-90 days post intervention period).

*Additional secondary outcome measures:*

*Diet Quality*

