- We will assess diet quality using the 10-item DSQ [11] with an addition question to assess traditional Diné food intake (*During the past month, how often did you eat traditional Diné foods (such as blue corn mush, steamed, roasted or dried corn, sumac berries, mutton, local varieties of squash or beans)*) at baseline and at the end of the intervention period.

*Food Security*

- We will evaluate baseline and 60-day rates of food insecurity utilizing the USDA Adult Food Security: Six Item short Form survey (USDA FSSM 6-Item).[12] At the 60-day evaluation, we will adapt the USDA FSSM 6-Item questionnaire to evaluate food insecurity within the last 2 (rather than 12 months).

*Indigenous Cultural Connectedness:*

- We will measure cultural connectedness utilizing a 6-question modified version of the validated Cultural Connectedness Scale-California (CCS-CA) at baseline and at 60 days.[13] This is a validated score, developed by Indigenous scholars to measure cultural connectiveness in Indigenous populations, and has been shown to correlate with physical health and be a social determinant of health.[14] This scale has previously been modified for use in Diné populations specifically by our group.

*Indigenous Nourishment Scale*

- We will evaluate the Indigenous Nourishment Scale (Measure A) [15], which is a scale developed through community-based methods in Indigenous communities to encompass multiple dimensions of nourishment. This scale offers an Indigenous framework to allow for health measurements rooted in Indigenous perspectives. We will evaluate Measure A of this scale at baseline and 60-days. We will score each question from 0 (never) to 6 (always) for a total score 0-54.

*Financial Stress*

- We will measure Financial Stress Scale at baseline and at 60 days using two questions:[16]

- How worried were you over the last 2 months about paying for housing (rent, mortgage, etc.)?
- How worried were you over the last 2 months about paying monthly bills?
  - All questions will be answered on a 4-point scale, where 1 = “not worried at all”, 2 = “not too worried”, 3 = “moderately worried”, and 4 = “very worried”

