#### *Implementation Outcomes: Fidelity, acceptability, feasibility, adoption:*

- We will evaluate the percentage of meals delivered successfully to the patient (or percentage of meals that were successfully picked up by the patient if picked up from the food pantry or other location).
- We will assess baseline dietary patterns through 3-day food diaries during week 1 and week 8 after enrollment. Additionally at 90 days, we will perform a survey to evaluate dietary patterns post intervention and adoption of any of the recipes/behavioral changes.
- We will evaluate patient satisfaction by evaluating the Net Promoter Score (i.e. how likely is it that you would recommend this program to a community member?) post-intervention.
- We will evaluate fidelity and compliance with survey at the end of the program to assess how many of the meals were consumed by the patient.
- We will perform semi-structured interviews of non-patient stakeholders (i.e. farmers that supplied produce, livestock farmers, food pantry) to assess acceptability and feasibility of providing produce for the meals, as well as the degree to which the program contributed to strengthening the local food system. We will also perform semi-structured interviews of primary care providers and a subset of patients. Semi-structured interviews will be guided by the Consolidated Framework for Implementation Research (CFIR), and we will explore multiple constructs within each CFIR domain that are hypothesized by the study team and based on existing literature to be relevant to acceptability and feasibility of the program.[17]

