Comparator: Those randomized to usual care will not receive any home delivery meals but will receive the recipes of healthy recipes that incorporate traditional local foods and educational booklet. They will also receive a gift bag for agreeing to participate in the study and a \$50 gift card upon completion of the study. Given ethical concerns about those not enrolled to receive the food is medicine intervention, after discussion with our community partners, we will provide 2 meals daily (14 meals weekly) for 4 weeks for all patients randomized to the control group after the study period (and outcome assessment) is complete if patients wish to receive meals and no safety concerns are identified.

Blinding of Intervention: Patients will be informed that they are enrolled in a program to receive medically and culturally tailored meals at home, and thus will not be blinded to their randomization status or participation in this trial. Providers will be not blinded to the intervention. Outcomes will be pulled from the EHR from study members, and those performing the analyses will be blinded to randomization status of the patient.

Enrollment Period: To allow time to coordinate the necessary operational and logistical infrastructure for meal delivery based on patient location/community and delivery mechanism, patients will be

consented and enrolled  $t=-45$  to  $t=-1$  days prior to the start of the intervention period ( $t=0$  for all patients). During this time, baseline assessment with surveys and lab work will take place. All patients will then start the study period (and outcome assessment period) at the same  $t=0$ . Any events that take place in the  $-45$  to  $-1$  days prior to the intervention period will not be included as an outcome. Summary of enrollment, intervention, and outcome assessment timeline is shown below.

[figure not shown]

Intervention Duration: The study team will implement the food intervention for 60 days.

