|                                                 | X                                                                                                                                                |                      |                      | X                                                                                                                                                |             |
|                                                 | - KCCQ12
- USDA Food insecurity
- DSQ10
- CCS Score
- Nourishment Scale
- Financial Stress Scale
- Exercise
- Health status |                      |                      | - KCCQ12
- USDA Food insecurity
- DSQ10
- CCS Score
- Nourishment Scale
- Financial Stress Scale
- Exercise
- Health status |             |
| Lab work                                        |                                                                                                                                                  |                      |                      |                                                                                                                                                  |             |
|                                                 | X                                                                                                                                                |                      |                      | X                                                                                                                                                |             |
|                                                 | - CMP
- CRP
- HbA1c
- Lipid panel
- Prealbumin                                                                                       |                      |                      | - CMP
- CRP
- HbA1c
- Lipid panel
- Prealbumin                                                                                       |             |
| Clinical measures                               |                                                                                                                                                  |                      |                      |                                                                                                                                                  |             |

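### Food-insecurity rates use different recall periods at baseline and day 60, the food diaries have no fixed anchor to the start of meals, and two laboratory outcomes are missing from the collection schedule

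*Protocol*

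**What the plan says.** **Food security** (Protocol, Phase II, Food Security). The instrument serves both visits: "We will evaluate baseline and 60-day rates of food insecurity utilizing the USDA Adult Food Security: Six Item short Form survey". The recall is shortened for the later visit only: "we will adapt the USDA FSSM 6-Item questionnaire to evaluate food insecurity within the last 2 (rather than 12 months". The Financial Stress items, in the same part of the protocol, use a 2-month window at baseline and at 60 days, for example "How worried were you over the last 2 months about paying monthly bills".

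**Food diaries** (Protocol, Implementation Outcomes). "We will assess baseline dietary patterns through 3-day food diaries during week 1 and week 8 after enrollment". Under Enrollment Period, patients are "consented and enrolled $t=-45$ to $t=-1$ days prior to the start of the intervention period", and the meals begin at t=0. The Enrollment paragraph of the Research Plan adds that "all baseline assessment (including consent, enrollment, baseline surveys and lab work) will occur in the enrollment period (-45 to 0 days prior". The Data Collection Timeline has no diary row; its only dietary row besides the DSQ-10 is a food survey at 90 days.

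**Laboratory outcomes** (Protocol, Endpoints). The secondary outcomes at baseline and 60 days include "albumin, prealbumin, creatinine, NT-proBNP, HbA1c, Total cholesterol, LDL-C, HDL-C, Triglycerides, CRP, urine albumin:creatinine ratio"; the Statement of Purpose gives the same list. The laboratory cell of the Data Collection Timeline, identical at both visits, reads "CMP - CRP - HbA1c - Lipid panel - Prealbumin".

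**The concern.** These are data-collection matters. A question not asked, a diary not kept or a sample not taken cannot be recovered at the analysis stage, and since every patient starts at one common t=0, a missed pre-meal baseline cannot be put right for later enrollees.

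- **Food security.** A patient who was food insecure eight months ago but not since counts as insecure on a 12-month recall and as secure on a 2-month recall. Set side by side, the two rates can show an improvement that reflects only the questionnaire. In a trial that delivers food, readers will look at that change early.
- **Diaries.** A before-and-after diet comparison needs a first diary free of study meals and a second one after a similar exposure in everyone. Timing from enrollment does not secure both.
- **Laboratory tests.** Site staff who work from the schedule would not order two of the named secondary outcomes, one of them a heart-failure biomarker.

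**Working it through.** The plan states no figure for food insecurity, so there is nothing of its own to reproduce. The checks below use its dates and lists, plus one illustration on assumed rates.

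**1. Recall length (assumed rates, no treatment effect).** Let p be the proportion insecure on a 12-month recall.

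- *All insecurity persistent:* the 2-month rate is also p, so nothing changes.
- *Episodes independent over time at a constant rate:* 2-month rate = 1 - (1 - p)^(2/12).
- *Half of the insecure patients persistent:* a fraction p/2 is insecure throughout. The other 1 - p/2 have a 12-month risk q = (p/2)/(1 - p/2). The 2-month rate is p/2 + (1 - p/2)[1 - (1 - q)^(2/12)].

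For p = 50%:
- Independent: 1 - 0.5^(1/6) = 0.109.
- Half persistent: q = 0.25/0.75 = 0.333, giving 0.25 + 0.75 × (1 - 0.667^(1/6)) = 0.25 + 0.049 = 0.299.

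| 12-month rate (assumed) | 2-month, all persistent | 2-month, half persistent | 2-month, independent |
|---|---|---|---|
| 30% | 30% | 18% | 6% |
| 50% | 50% | 30% | 11% |
| 70% | 70% | 43% | 18% |

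The apparent fall runs from zero to 52 points (70% to 18%), depending wholly on assumptions that the documents cannot settle. Its direction is not in doubt: it is a fall or no change.

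**2. Diary dates.** Count the enrollment day e as the first day of week 1. Week 1 is then days e to e+6, and week 8 is days e+49 to e+55.

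| Reading of enrollment | Week 1 | Week 8 |
|---|---|---|
| Earliest enrollee, e = -45 | -45 to -39 | +4 to +10 |
| Latest enrollee, e = -1 | -1 to +5 | +48 to +54 |
| Enrollment taken as t=0 | 0 to 6 | 49 to 55 |

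On the first reading, the start of week 8 varies by 44 days (+4 to +48) in a 60-day intervention. Patients enrolled on day -2 or -1 also have fewer than three days before meals start, too few for a 3-day diary. On the t=0 reading the follow-up time is common, but in the meal arm the first diary is kept on study meals. Neither reading gives every patient both a pre-meal baseline and a common follow-up time.

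**3. Outcome list against schedule.**

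| Named outcome | Scheduled test that supplies it |
|---|---|
| Albumin, creatinine | CMP |
| Prealbumin | Prealbumin |
| HbA1c | HbA1c |
| Total, LDL and HDL cholesterol, triglycerides | Lipid panel |
| CRP | CRP |
| NT-proBNP | none |
| Urine albumin:creatinine ratio | none |

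The gap is the same in both columns, so it is a conflict between the outcome list and the schedule, not a difference between the visits.

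**The case against.** **Food security.** Shortening the recall at day 60 has an evident reason: a 12-month question asked then would mostly cover time before the intervention (about 10 of 12 months). The randomized contrast at day 60 uses one form in both arms and is sound. The Statistical Analysis section gives laboratory values, CCS and KCCQ as its examples for within-group testing, and food security is not among them. All of this stands. It limits the fault to the before-and-after rates, which the protocol nevertheless says it will evaluate. The 12-month baseline recall is implied, not stated.

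**Diaries.** The protocol is loose about its time origin elsewhere: the sample-size paragraph counts 90 days from randomization where other sections use t=0. Week 8 may well mean study week 8. A reader might infer that some follow-up diaries will certainly fall in the second week of meals; the text does not establish that, only that the anchor is open. Nor is a diary after enrollment wrong in itself, since baseline work is planned inside the enrollment period. What survives is that both readings fail on one requirement or the other. A reader might also infer that diet change cannot be interpreted at all. That goes too far: the DSQ-10, with its added traditional-food item, is taken at baseline and at the end of the intervention and is unaffected.

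**Laboratory tests.** Two sections name both tests at both visits, and Endpoints gives a collection window for the 60-day laboratory work. It does not follow that they will go uncollected; that would need staff to use the table alone. The contradiction still has to be removed.

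**Conclusion.** The point holds in limited form and should be corrected before data collection.

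- **Food security:** the baseline and 60-day rates are not comparable if, as the wording implies, baseline uses a 12-month recall. They could show a fall in both arms with no true change. No size can be given from the documents. The illustration spans no fall to a very large one, and a narrower range would rest on assumed rates. It would be wrong to conclude that the trial cannot assess food security: the day-60 comparison between arms remains valid.
- **Diaries:** the anchor is ambiguous, and neither reading yields both a pre-meal baseline and a common follow-up time for everyone. The 44-day spread applies only if weeks are counted from each patient's own enrollment. The diaries are an implementation outcome.
- **Laboratory tests:** NT-proBNP and urine albumin:creatinine ratio are the only named laboratory outcomes without a scheduled test, at either visit.

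None of this affects the primary outcome or the sample size.

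**What to change.** 1. **Food security.** Ask the six items with a 2-month reference period at both baseline and day 60. Keep the 12-month version at baseline to define the food-insecurity subgroup. Cost: six extra baseline questions.
2. **Diaries.** Collect the first diary in the enrollment period before t=0 and the second in week 8 counted from t=0, and add both to the Data Collection Timeline. Cost: a change of wording and a new row; late enrollees need enough days before t=0 to complete the first diary.
3. **Laboratory tests.** Add NT-proBNP and urine albumin:creatinine ratio to the baseline and 60-day laboratory rows. The home-visit fallback for the 60-day laboratory work mentions blood only, so say there how the urine sample is obtained. Cost: a correction to the schedule, as both tests are already named outcomes.

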#### *Intervention characteristics:*

- We will evaluate the following in partnership with Tocabe:
  - % of meals that include locally sourced ingredients
  - % of food supply sourced by Diné producers/suppliers/farmers
  - % of meals sourced by Native suppliers/farmers

#### *Implementation Outcomes: Fidelity, acceptability, feasibility, adoption:*

- We will evaluate the percentage of meals delivered successfully to the patient (or percentage of meals that were successfully picked up by the patient if picked up from the food pantry or other location).
- We will assess baseline dietary patterns through 3-day food diaries during week 1 and week 8 after enrollment. Additionally at 90 days, we will perform a survey to evaluate dietary patterns post intervention and adoption of any of the recipes/behavioral changes.
- We will evaluate patient satisfaction by evaluating the Net Promoter Score (i.e. how likely is it that you would recommend this program to a community member?) post-intervention.
- We will evaluate fidelity and compliance with survey at the end of the program to assess how many of the meals were consumed by the patient.
- We will perform semi-structured interviews of non-patient stakeholders (i.e. farmers that supplied produce, livestock farmers, food pantry) to assess acceptability and feasibility of providing produce for the meals, as well as the degree to which the program contributed to strengthening the local food system. We will also perform semi-structured interviews of primary care providers and a subset of patients. Semi-structured interviews will be guided by the Consolidated Framework for Implementation Research (CFIR), and we will explore multiple constructs within each CFIR domain that are hypothesized by the study team and based on existing literature to be relevant to acceptability and feasibility of the program.[17]

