## 1.B Supply Chain and Meal Delivery Logistics

As part of Phase I, we established and secured a supply chain for meals, and secured logistics for meal delivery, particularly for those living rurally on the reservation. Among a sample of n=22 HF patients, we found that 95% of patients had PO boxes (without a physical address/mailbox). Given this, we have partnered with the Gallup Food Pantry, and will have frozen meals prepared, packaged, and delivered to the Gallup Food Pantry in bulk as a central food hub, with subsequent patient distribution. Patients that live locally and are able to pick up meals will come pick up meals weekly. Those who are unable to pick up meals (or do not come for their meals), will have meals delivered weekly through various mechanisms (per patient preference) that were tested and deemed successful in our pilot trial. These include delivery to a minihub (Chapter House, Tohatchi Health Clinic) for pick-up, delivery by community health representative (CHR) or nurse, and peer delivery (pick up at food pantry and delivery by another participant living in same community for peer that is unable to pick up). For those without refrigeration, meals will be delivered to local chapter houses, and patients will pick up 3-day supply of meals in freezer boxes. In addition to refrigeration, we will also assess and address household infrastructure (e.g. ability to store and heat meals). We developed these logistical plans and evaluated them in our pilot feasibility trial, which has informed operationalizing our phase II comparativeness effectiveness trial.

[figure not shown]

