#### *Per-Protocol Analysis and Compliance Adjustment Analysis*

We will also incorporate a per-protocol analysis to assess the impact of adherence on study outcomes, ensuring a robust evaluation of the intervention's effectiveness beyond intention-to-treat (ITT) analysis.

Per-Protocol Analysis Strategy: Participants will be included in the per-protocol cohort if they meet the following compliance criteria:

- $\geq 70\%$  adherence to meal delivery (defined as receiving and consuming at least 42 of the 60 intervention meals).
- Completion of baseline and 60-day assessments and lab parameters.
- The per-protocol population will be analyzed separately to determine if high adherence to the medically tailored meal intervention is associated with improved clinical outcomes compared to the usual care group.
- Results will be compared to the intention-to-treat (ITT) analysis to identify potential differences in effect size due to adherence variability.

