#### 3. Multiple Imputation for Missing Compliance Data:

- Missing adherence data will be handled using multiple imputation techniques to minimize bias and maintain analytical power.

Subgroup: We perform subgroup analysis based on EF (LVEF <50, and >50%), gender, age (<65 and ≥65 years), and food insecurity (those with low or very low food security vs. food secure). We will also analyze for significant changes in weight in those with obesity (BMI ≥ 30mg/kg), HbA1c among those with diabetes (HbA1c ≥ 7), and cholesterol (total, triglycerides and LDL) among those with baseline hyperlipidemia.

Semi structured interviews will be audio-recorded and transcribed for thematic analysis. Transcripts will be analyzed using an integrated approach, an iterative process to determine themes and patterns present in the data.[18] The interviewers will develop the initial codebook together, and then will independently dual code subsets of the transcripts to identify common themes and iteratively develop a final codebook, with periodic assessment of inter-rater reliability. We will follow the consolidated criteria for reporting qualitative research (COREQ) guidelines.[19]

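### Meals eaten are counted only by one recall survey at the end of the program, an imprecise basis for the sharp adherence cut-off in the per-protocol and compliance-adjusted analyses

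*Protocol*

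**What the plan says.** Under Per-Protocol Analysis and Compliance Adjustment Analysis, a patient needs at least 70% adherence, "defined as receiving and consuming at least 42 of the 60 intervention meals". The same list also requires "Completion of baseline and 60-day assessments and lab parameters".

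Under Implementation Outcomes, receipt and eating are measured separately:

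- Receipt: "We will evaluate the percentage of meals delivered successfully to the patient", or the share picked up.
- Eating: "We will evaluate fidelity and compliance with survey at the end of the program to assess how many of the meals were consumed". This is the only item that asks how many meals were eaten.
- Diaries: "We will assess baseline dietary patterns through 3-day food diaries during week 1 and week 8 after enrollment". They describe dietary patterns, and nothing links them to the meal count.

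The Data Collection Timeline lists no meals-consumed item. On distribution, section 1.B says "Patients that live locally and are able to pick up meals will come pick up meals weekly", with weekly delivery through a mini-hub, a health worker or a peer for the others. On gaps in the data, "Missing adherence data will be handled using multiple imputation techniques to minimize bias and maintain analytical power".

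**The concern.** The adherence rule needs a count of meals eaten, and that count is one patient's memory of about two months. Two things follow.

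First, recall error near a threshold moves patients across it in both directions, so the adherent and non-adherent groups are partly mixed.

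Second, the report is collected around day 60 of a 90-day outcome period, from patients who know their assignment. For some of them an admission or emergency visit will already have happened and could colour the answer.

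The per-protocol cohort, the inverse probability weights, the instrumental-variable estimate and the imputation of missing adherence all use this variable. The protocol intends to read a difference between per-protocol and intention-to-treat results as the effect of adherence. Part of that difference could instead come from the measurement. The choice of instrument and its timing are set in the protocol, and no later analysis plan can recover weekly counts that were never collected.

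**Working it through.** **1. The plan's own cut-off.** 42 / 60 = 70%, so the rule agrees with itself. The Phase II section, however, supplies two meals a day over 60 days: 2 × 60 = 120. Against 120 meals, 42 is 42 / 120 = 35%, and 70% would be 0.70 × 120 = 84. Both readings are carried forward, as the protocol does not settle between them.

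**2. Other sources of intake data.** Two 3-day diaries cover 6 of 60 days (10%), at most 2 × 6 = 12 of 120 meals. Delivery and pick-up records give an upper limit on meals eaten, not the number eaten.

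**3. Misclassification at the cut-off.** All inputs here are assumptions, since the protocol gives none: true adherence normal with mean 70 or 80% and SD 15 or 20 points; reported adherence equal to true plus a normal error with mean zero and SD 10, 15 or 20 points; both limited to 0-100%. Entries are the percentage of meal-arm patients on the wrong side (400,000 simulated patients per setting).

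| True mean / SD | Cut-off 70%, error SD 10 / 15 / 20 | Cut-off 35%, error SD 10 / 15 / 20 |
|---|---|---|
| 70 / 15 | 18.7 / 24.9 / 29.5 | 2.2 / 4.7 / 7.9 |
| 70 / 20 | 14.8 / 20.6 / 25.3 | 4.0 / 6.6 / 9.8 |
| 80 / 15 | 15.6 / 21.7 / 26.5 | 0.6 / 1.7 / 3.6 |
| 80 / 20 | 13.2 / 19.0 / 23.6 | 1.7 / 3.2 / 5.3 |

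The ranges are 13-30% at a 70% cut-off and 0.6-10% at 35%. Among patients classed adherent, 8-30% would truly be below a 70% cut-off, and under 2% below a 35% one.

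Hand check: when the true mean equals the cut-off, the misclassified share is arctan(error SD / true SD) / π. For 20 and 15 this is arctan(1.333) / π = 0.927 / 3.142 = 29.5%; for 10 and 20 it is arctan(0.5) / π = 0.464 / 3.142 = 14.8%. Both match the table.

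**4. Events before the survey.** Inputs are the 90-day rates of 13% and 29% and the total of 204 from Sample Size Determination, so 102 per arm. Assume a constant hazard and a 90-day period that starts with the intervention. The proportion with a first event by day 60 is 1 − (1 − p)^(60/90):

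- p = 0.13: 1 − 0.87^(2/3) = 8.9%, or 9 of 102.
- p = 0.29: 1 − 0.71^(2/3) = 20.4%, or 21 of 102. This is the control rate, so it applies to the meal arm only if the meals have no effect.

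These are patients whose report would follow an event. They are not a count of missing surveys.

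**The case against.** **The survey gives a count.** A reader might infer that an end-of-program survey cannot supply the number the rule needs. The document does not support that: asking how many meals were eaten is the survey's stated purpose, and delivery records cap the answer. The defect is imprecision.

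**Missingness after an event is not documented.** A reader might also infer that the survey will be missing mainly in patients who had an event. Nothing in the protocol says so. The outcome includes emergency visits for any cause, and a visit in week 3 does not prevent a survey at day 60. Patient-reported measures can be taken by phone, reminders are planned, and outreach extends to family contact and a home visit. Event-related missingness remains possible, but its size is unknown.

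**The completion criterion limits what a weekly log can do.** Per-protocol entry also requires complete 60-day assessments and laboratory results. A patient who died or dropped out before then is excluded whatever the meal count, and neither imputed adherence nor weekly counts would bring that patient back.

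**Scope and remedy.** The primary analysis is by intention to treat, with outcomes taken from records, so only supplementary analyses are touched. Weekly answers would still be self-report by unblinded patients, and peer or mini-hub pick-up may involve no weekly staff contact.

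All four objections stand and limit the point. What remains is that one long recall is the only stated source for a variable that is then cut at a threshold.

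**Conclusion.** The point holds as a low-severity weakness in measurement. Under the assumptions shown, about 13-30% of meal-arm patients would be misclassified at a 70% cut-off, but only about 0.6-10% if 42 meals is read against the 120 supplied. The size therefore depends on a contradiction between the Phase II meal supply and the per-protocol definition, which must be reconciled first. It also rests on assumed adherence and recall-error distributions, and a smaller recall error would reduce it. The consequence is confined to the per-protocol and compliance-adjusted results and to their comparison with intention to treat.

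**What to change.** First reconcile the number of meals in the per-protocol definition with the number supplied in Phase II.

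Then, under Implementation Outcomes, add one question at each existing weekly pick-up or delivery: how many of the previous supply's meals the patient ate. Record it on the same log as meals received. Where there is no staff contact, as with peer or mini-hub pick-up, collect it by a brief text or phone call. Use the summed weekly counts for the adherence classification and the compliance models, and keep the end-of-program survey as a check.

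Recall then covers about a week instead of two months. For a patient who stops early, counts up to the last contact become available to the compliance-adjusted analyses. They do not restore that patient to the per-protocol cohort if the 60-day assessments are incomplete.

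The cost is one question and one log column. The downsides are a little more data entry, possible reactivity to being asked each week, and some extra contact in the meal arm only, which in an open-label trial of health-care use should be kept brief and reported. The change has to be in place before the common start date.
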